### Participants

Patients with flexor spasticity of the upper limb after stroke (Table 2).

**Table 2 T2:** Flow chart of the study.

**Items/Time points**	**Enrollment**	**Allocation**	**Post-allocation**		
	***-t1***	**Baseline**	***t1***	***t2***	***t3***
Basic medical history	×				
Eligibility screen	×				
Informed consent	×				
Allocation(Group A/Group B)		×			
Intervention(Group A/Group B)		×			
Assessments	MAS		×	×	×	×
	H reflex		×			×
	MCV		×			×
	RMS		×	×	×	×
	iEMG		×	×	×	×
	CR		×	×	×	×
	MyotonPRO		×	×	×	×
	IRT		×	×	×	×

*Group A, active rESWT; Group B, sham-placebo rESWT; MAS, Modified Ashworth Scale; MCV, Motor nerve conduction velocity; RMS, Root mean square value; iEMG, Integrated electromyogram; CR, co-contraction ratio; IRT, Infrared Thermal Imaging; t1/ t2/ t3, at 24 hours after the first/ second/ third radial extracorporeal shock wave therapy*.

### Recruitment

Direct recruitment from Zhujiang Hospital.

### Sample Size Calculation

The known effectiveness of poststroke spasticity treatment using conventional methods is 64.5%, whereas preliminary experiments with ESWT have shown expected effectiveness of 80%, with two-tailed tests of a significance level of α = 0.05 and β = 0.1, which is expected to fall off at a rate of 10%, using professional software Advisor nQuery sample size estimation, for a sample size of 45 cases in each group, which can be considered as a loss rate of approximately 10%. Therefore, for this study, a sample size of 50 cases in each group was decided on, with a total sample size of 100 cases.

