### Interventions

**Active Radial Extracorporeal Shock Wave Therapy Intervention (Group A):** An rESW device (Power Shocker LGT-2510A, Guangzhou Longest Science & Technology Co., Ltd., China) was used for shock wave therapy. Study participants were treated in the supine position on the area of the biceps brachii, the flexor carpi radialis, and the pronator teres muscle after their affected side has been marked and the skin has been cleaned by soaking with alcohol.

The coupling gel as a contact medium is evenly applied onto the treatment probe to reduce tissue resistance, and a medium- to high-intensity pressure was applied to keep the probe close to each muscle belly. The following protocol is to be used: 2,000 shots, an energy flux density of 0.03 mJ/mm^2^, a pressure of 0.2 MPa (two bars), and a frequency of 8 Hz is delivered to each marked position, for a total of three rounds of treatment, once in 3 days.

**Sham Radial Extracorporeal Shock Wave Therapy Intervention (Group B):** The protocol to be used is the same as that of “group A,” except that pressure is one bar and no coupling gel is used on the treatment site, whereas a thick layer of gauze is placed between the skin and the probe instead, with no pressure applied.

The physiotherapist who is to perform the intervention should have received standardized training and must be familiar with the process and details of the intervention. The patients are all required to undergo the same routine therapeutic program (including common physical therapy and occupational therapy).

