### Outcome Measures

#### Primary Outcome Measure: Modified Ashworth Scale

The scale is graded in six stages, ranging from 0 (no increase in tone) to 4 (limb rigid in flexion or extension). For the convenience of statistical analysis, a MAS grade of 1+ is to be substituted with a value of 2, whereas grades 2, 3, and 4 are to be substituted with values of 3, 4, and 5, respectively Table 1.

**Table 1 T1:** Definitions of MAS for grading muscle spasticity.

**Grade**	**Modified ashworth scale (28)**	**Values**
0	No increase in muscle tone;	0
1	Slight increase in muscle tone, manifested by a catch and release or by minimal resistance at the end of the range of motion when the affected part is moved in flexion or extension;	1
1+	Slight increase in muscle tone, manifested by a catch, followed by minimal resistance throughout the remaining (less than half) range of motion;	2
2	More marked increase in muscle tone through most of the range of motion, but affected part easily moved;	3
3	Considerable increase in muscle tone, passive movement difficult;	4
4	Affected part(s) rigid in flexion or extension.	5

*For convenience of statistical analysis, a Modified Ashworth Scale grade 1+ is to be substituted with a value of 2, and grade 2, 3 and 4 are matched to 3, 4, and 5, respectively*.

(1) Recovery: Muscle tension had completely returned to normal;(2) Obvious effect: The muscle tension had not returned to normal, but muscle tension had decreased by two levels;(3) Effective: Muscle tension had decreased by 1 level;(4) Inefficacy: No change in muscle tone pre- and posttreatment.

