### Statistical Methods

The primary comparisons for MAS will be made using repeated measures mixed-effect model with terms of treatment, time, and corresponding baseline values as covariates. We will first examine the intervention by time interaction and then proceed to the main effects model with only group and time.

Repeated analysis of variance with *post-hoc* test will be used to compare changes between active rESWT intervention and sham rESWT intervention groups from baseline to the end of follow-up when data are normally distributed, and the Mann–Whitney U-test will be used when data are not normally distributed. A chi-square test will be used for dichotomous variables.

In secondary analyses, repeated measures mixed model will also be used to examine the associations between treatments and repeated measures outcomes. Additionally, linear regression and/or logistic regression analyses will be used to assess the associations between treatments and changes or increases in outcomes from baseline to the end of follow-up in univariate and multivariate modeling adjusted for relevant covariates.

All data will be analyzed using intention-to-treat principles. Multiple imputation by chained equations will be used to address missing data caused by loss to follow-up and non-responses. Per protocol analyses will also be performed in the participants who complete other assessments, including Hmax/Mmax, MCV, RMS, iEMG, CR, MyotonPRO, and IRT. Statistical analysis will be performed using SPSS software (version 20.0) and the significance level set at *p* < 0.05.

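### The stated 90% power does not describe the primary mixed-model analysis of MAS, and it does not hold for the two-proportion comparison it was computed from either (about 37% with 45 per group)

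*Protocol article*

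**What the plan says.** All references are to the protocol article.

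- **Sample Size Calculation.** The control assumption is "The known effectiveness of poststroke spasticity treatment using conventional methods is 64.5" (per cent). For the active arm, "preliminary experiments with ESWT have shown expected effectiveness of 80" (per cent). The error rates are "two-tailed tests of a significance level of α = 0.05 and β = 0.1", that is, 90% power. Dropout is 10%, and the result is given as "for a sample size of 45 cases in each group", taken up to 50 per group and 100 in total. The word effectiveness is not defined there, and no MAS difference, SD or correlation appears.
- **Statistical Methods.** "The primary comparisons for MAS will be made using repeated measures mixed-effect model", with treatment, time and the baseline value in the model. The treatment-by-time interaction is examined first, followed by a main-effects model with group and time. A chi-square test is mentioned only for dichotomous variables in general.
- **Primary Outcome Measure: Modified Ashworth Scale.** The scale is recoded 0 to 5. The same section also lists four response categories, among them "Effective: Muscle tension had decreased by 1 level". It does not state what role they play beside the score.

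**The concern.** A sample size statement should give the power of the analysis on which the trial will be judged. Here the inputs are two proportions, while the declared primary comparison is a model of repeated scores. Nothing in the article connects the two. The reader is told that the trial has 90% power but cannot tell what MAS difference it could detect.

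The figure also matters in its own right. If the trial ends without a significant result, the 90% claim would invite the reading that a 15.5-point difference in effectiveness (80% minus 64.5%) has been more or less ruled out. At the planned size that reading would be wrong.

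**Working it through.** **Inputs from the Sample Size Calculation section:** p1 = 0.645, p2 = 0.80, difference 0.155, two-sided alpha 0.05 (z = 1.960), power 90% (z = 1.282), 10% dropout, 45 then 50 per group. Allocation is equal (Randomization section).

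**1. Reproducing the plan's figure.** Two-proportion formula, pooled variance under the null:

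n = [(1.960·A + 1.282·B) / (p2 − p1)]²

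- Mean rate = (0.645 + 0.80)/2 = 0.7225
- A = √(2 × 0.7225 × 0.2775) = √0.4010 = 0.6332
- B = √(0.645 × 0.355 + 0.80 × 0.20) = √0.3890 = 0.6237
- n = [(1.2411 + 0.7993)/0.155]² = 173.3, so **174 per group**, or 174/0.9 = 193.3, so 194 after dropout

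Other versions tried for the size before dropout:

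| Version | n per group |
|---|---|
| 90% power, unpooled variance | 171 |
| 90% power, arcsine | 173 |
| 90% power, continuity correction | 186 |
| 90% power, one-sided | 142 |
| 80% power, two-sided | 130 |
| 80% power, one-sided | 103 |
| One-sample formula, 90% / 80% power | 88 / 68 |

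None gives 45. Only the dropout step reproduces: 45/0.9 = 50.

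**2. Power of the two-proportion test at the planned size.** Power = Φ[((p2 − p1)√n − 1.960·A)/B]

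- n = 45: (1.0398 − 1.2411)/0.6237 = −0.323, so **37%** (exact enumeration of the chi-square test: 39%)
- n = 50: (1.0960 − 1.2411)/0.6237 = −0.233, so **41%** (exact: 41%)

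With 45 per group and 64.5% in the control arm, 90% power would need about 92% in the active arm.

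**3. What 45 per group can detect on the MAS score.** The article gives no SD or correlation, so these are illustrations. From the non-central t distribution, an unadjusted comparison at one visit has 90% power for 0.691 SD. Let ρ be the correlation between any two visits, baseline included, assumed equal.

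- Baseline-adjusted contrast at t3 alone: 0.691 × √(1 − ρ²)
- Baseline-adjusted group effect averaged over t1, t2 and t3: 0.691 × √[(1 + 2ρ)/3 − ρ²]

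| Assumed ρ | t3 alone | Mean of t1 to t3 |
|---|---|---|
| 0.3 | 0.691 × √0.91 = 0.66 SD | 0.691 × √0.443 = 0.46 SD |
| 0.6 | 0.691 × √0.64 = 0.55 SD | 0.691 × √0.373 = 0.42 SD |
| 0.8 | 0.691 × √0.36 = 0.41 SD | 0.691 × √0.227 = 0.33 SD |

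The SD fixes what this means in MAS points. For the unadjusted single-visit comparison (0.683 SD by the normal approximation), assumed SDs of 0.6, 0.8, 1.0 and 1.2 give detectable differences of 0.41, 0.55, 0.68 and 0.82 points.

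**The case against.** The strongest reply is that the article does name its primary analysis, and that a repeated score with baseline adjustment usually uses the data better than a responder rate. On that view, sizing on proportions is only a rough planning device. Much of this stands, and it limits what can be claimed.

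- *No analysis is identified as decisive.* A reader might infer this from the response categories listed under the primary outcome. The Statistical Methods section does not support it: the mixed model is called the primary comparison, and no effective rate is. What remains is a smaller gap, that the role of the categories is not stated.
- *The MAS analysis is underpowered.* This does not follow. Its detectable difference depends on an SD, a correlation and a contrast that the article does not give. The article also never names t3 as the contrast, so figures for t3 alone may not describe the model that will be fitted.
- *64.5% is the wrong rate for the sham arm.* The Interventions section says "The patients are all required to undergo the same routine therapeutic program", so conventional methods may well describe the control arm's background care. Whether the rate fits depends on a source not shown.
- *The 90% belongs to a responder test.* Reading effectiveness as the listed MAS categories is an inference. Under any of the two-proportion calculations tried, the stated inputs do not give 90% power at this size.

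The reply does not rescue the power statement. A planning device still has to follow from its inputs, and this one does not. Nor is this a detail left to a fuller document: the article states both the justification and the primary analysis, and they do not match.

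**Conclusion.** The point holds in this form. The 90% power claim does not describe the primary mixed-model comparison of MAS scores, for which no power can be derived from the article. It is also wrong for the comparison of 64.5% with 80%: about 37% with 45 per group and about 41% with 50, against about 174 per group needed for 90%. These figures use only the plan's own inputs and do not depend on the choice of formula to any degree that matters.

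The MAS-scale figures at 45 per group and 90% power are about 0.66 to 0.41 SD for t3 alone, or 0.46 to 0.33 SD averaged over t1 to t3. They rest on assumed correlations of 0.3 to 0.8, taken as equal between all visits. They show why the contrast must be named, not that the trial is too small.

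**What to change.** Keep the total at 100 and make three changes.

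1. In Sample Size Calculation, withdraw the 90% claim for 64.5% versus 80% and state about 37% for 45 evaluable patients per group.
2. In the same section, add the detectable MAS difference in points for the treatment contrast that the mixed model will actually report. Name that contrast: the group effect over t1 to t3, or one visit. Use an SD pooled without group labels from patients already recruited (50 at submission, per Trial Status) and show a range of correlations.
3. In the primary outcome section, confirm that the MAS score analysed by the mixed model is the primary endpoint and that the four response categories are secondary.

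The cost is a less favourable published power figure, a small blinded SD calculation, and a protocol amendment, which under the Harm and Audit section needs ethics committee approval. Naming a responder rate as primary instead would not repair the plan at this size, since it would need about 174 per group before dropout. The changes should be made before unblinding.

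### The stated 45 per group does not give 90% power for 64.5% versus 80% effectiveness: those inputs need about 174 evaluable per group, and 45 give about 37% power for that comparison.

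*Protocol article*

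**What the plan says.** The Sample Size Calculation section gives all the inputs and the result in one paragraph.

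- Control rate: "The known effectiveness of poststroke spasticity treatment using conventional methods is 64.5" (percent).
- Experimental rate: "preliminary experiments with ESWT have shown expected effectiveness of 80" (percent).
- Error rates: "two-tailed tests of a significance level of α = 0.05 and β = 0.1", that is, 90% power.
- Loss: "which is expected to fall off at a rate of 10" (percent).
- Result: "using professional software Advisor nQuery sample size estimation, for a sample size of 45 cases in each group".
- Decision: "a sample size of 50 cases in each group was decided on, with a total sample size of 100 cases".

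The Randomization section confirms equal groups of 50. Under Statistical Methods, the primary comparison is a repeated-measures mixed-effect model on MAS with baseline adjustment, and a chi-square test is reserved for dichotomous variables.

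**The concern.** A difference of 15.5 percentage points between two proportions in this range normally takes well over 100 patients per group to detect with 90% power, so 45 looks too small by a wide margin. The inputs and the output are both printed and can be checked against each other, so this is not a detail left to a fuller document.

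The 90% figure is the only power statement in the article. If it is wrong, a reader who sees a non-significant responder result may take it as good evidence against the assumed effect, on the strength of a power that the design does not have for that comparison.

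**Working it through.** **Inputs** (Sample Size Calculation; 1:1 allocation from Randomization): p1 = 0.645, p2 = 0.80, difference d = 0.155, two-sided alpha 0.05 (z = 1.960), beta 0.1 (z = 1.2816), loss 10%.

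**Step 1: the loss adjustment.** 45 / (1 − 0.10) = 50. The step from 45 to 50 is correct, so any error lies in the 45.

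**Step 2: the base figure, pooled two-proportion formula.**

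n = [z(alpha)·√(2·p̄·(1−p̄)) + z(beta)·√(p1(1−p1) + p2(1−p2))]² / d², with p̄ = (0.645 + 0.80)/2 = 0.7225.

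- √(2 × 0.7225 × 0.2775) = √0.40099 = 0.6332
- √(0.645 × 0.355 + 0.80 × 0.20) = √0.388975 = 0.6237
- n = (1.960 × 0.6332 + 1.2816 × 0.6237)² / 0.155² = (1.2411 + 0.7993)² / 0.024025 = 173.3, so **174 per group**

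The stated 45 is not reproduced; 174/45 is about 3.9. With 10% loss, 174/0.9 = 193.3, so 194 per group or 388 in total.

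**Step 3: other two-group variants.**

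| Variant | Evaluable per group |
|---|---|
| Two-sided, 90% power, pooled | 174 |
| Two-sided, 90% power, unpooled | 171 |
| Two-sided, 90% power, arcsine | 173 |
| Two-sided, 90% power, continuity-corrected | 186 |
| One-sided, 90% power, pooled | 142 |
| Two-sided, 80% power, pooled | 130 |
| One-sided, 80% power, pooled | 103 |
| One-sided, 80% power, unpooled (smallest found) | 101 |

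The last four rows relax the stated alpha or beta. None comes near 45.

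**Step 4: power at the planned size.** Power = Φ{[d·√n − z(alpha)·√(2·p̄·(1−p̄))] / √(p1(1−p1) + p2(1−p2))}.

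- n = 45: (0.155 × 6.708 − 1.2411) / 0.6237 = −0.323, so power is **37.3%**
- n = 50: (0.155 × 7.071 − 1.2411) / 0.6237 = −0.233, so power is **40.8%**

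Exact enumeration agrees. The uncorrected chi-square test has 38.8% at 45 and 41.3% at 50; Fisher's exact test has about 29% and 34%. A one-sided test at 45 per group would still reach only 49.9% (normal approximation).

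**Step 5: what 45 per group can detect.** Solving the formula in Step 4 for p2 with p1 = 0.645:

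- 90% power: p2 = 0.920, a difference of 27.5 points
- 80% power: p2 = 0.891, a difference of 24.6 points

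**Step 6: precision.** At the assumed rates with 45 per group, the 95% confidence interval half-width is 1.96 × √(0.388975/45) = 0.182, or about 18 points. An observed difference of zero would thus leave 15.5 points inside the interval. Holding that half-width fixed, the estimate would have to favour sham by more than about 2.7 points (18.2 − 15.5) before 15.5 was excluded.

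**The case against.** The strongest objection is that the 37% does not describe the trial's primary analysis. Statistical Methods makes that a baseline-adjusted mixed model on the MAS, scored 0 to 5 and measured after each of three sessions. Such a model may have quite different power from a comparison of two proportions. This stands. A reader might infer that the whole trial has 37% power, or that any null result from it would be close to uninformative. The document does not support either. It gives no MAS difference, standard deviation or correlation, so the power of the primary model cannot be computed. Even for responders, a null result would bear on effects much larger than 15.5 points.

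A second objection is that 45 might come from some other calculation. A one-sample test of 80% against a fixed 64.5%, with the same alpha and beta, gives (1.960 × √0.228975 + 1.2816 × √0.16)² / 0.024025 = 87.6, so 88, or 44 if split across two groups. It would therefore go too far to say that no calculation lands near 45. But this origin is a guess, and the method is not valid for comparing two randomised groups.

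Neither objection rescues the paragraph as printed.

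**Conclusion.** The sample-size statement is wrong as written. With the stated rates, alpha and beta, about 174 evaluable patients per group are needed, nearly four times the 45 given. The binary effectiveness comparison has about 37% power at 45 per group and about 41% at 50, against the stated 90%. If the assumed 15.5-point effect is real, that comparison would miss it about 63% of the time at 45 per group, and a non-significant result would generally not exclude it.

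This rests only on inputs printed in the article, on equal allocation, and on a standard two-group comparison of proportions. The choice among standard formulas moves the required number between 171 and 186 and does not change the conclusion. The size of the shortfall applies to the effectiveness comparison used for sizing and does not carry over to the primary MAS model.

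**What to change.** Keep N = 100 and correct the Sample Size Calculation paragraph:

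- Withdraw the claim of 90% power for 64.5% versus 80%.
- State that 45 evaluable patients per group give about 37% power for 64.5% versus 80% (about 41% if all 50 per group are evaluable).
- State that 45 per group give 90% power only for about 92% versus 64.5%, a difference of about 27.5 points.
- Say plainly that this corrects the statement and does not restore the power.

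If the sponsor holds a MAS difference, standard deviation and within-patient correlation, it may add a power figure for the primary mixed model. That is optional, since the article does not contain those inputs.

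The cost is a change of wording and a published figure that becomes less favourable. No extra patients are needed.

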### Randomization

Eligible patients are to be numbered sequentially based on enrollment sequence and randomly assigned to group A (active rESWT) or group B (sham-placebo rESWT), with a total of 50 patients in each. Random numbers are to be generated using a computer software program run by an external statistician. Each of the random numbers and the group assignment are to be written on a piece of paper and enclosed in a sealed envelope.

### Blinding

This study uses a double-blinded design, in which interventions are performed by one physiotherapist and patients are evaluated by another physician who is unaware of the treatment or grouping. Neither of them will participate in the subsequent data analysis.

After the statistical judgment is completed, unblinding will be performed to expose the experimental group and the control group. In general, emergency unblinding is not considered.

### Data Collection Methods

The evaluation index is to be collected before and after treatment is performed on all patients, with raw data recorded on case report forms (CRFs) in a timely, complete, accurate, and clear manner. To improve subject compliance, subjects who can complete the entire procedure in accordance with the protocol are to be provided with additional rehabilitation assessments and rehabilitation recommendations. If a participant chooses to withdraw, they will be asked to provide reasons, and the reasons for withdrawal are to be recorded.

### Data Management

An EPIDATA 3.2 database will be used to manage data, for which input and proofreading will be performed by two researchers independently, leading to double data entry and storage.

### Statistical Methods

The primary comparisons for MAS will be made using repeated measures mixed-effect model with terms of treatment, time, and corresponding baseline values as covariates. We will first examine the intervention by time interaction and then proceed to the main effects model with only group and time.

Repeated analysis of variance with *post-hoc* test will be used to compare changes between active rESWT intervention and sham rESWT intervention groups from baseline to the end of follow-up when data are normally distributed, and the Mann–Whitney U-test will be used when data are not normally distributed. A chi-square test will be used for dichotomous variables.

In secondary analyses, repeated measures mixed model will also be used to examine the associations between treatments and repeated measures outcomes. Additionally, linear regression and/or logistic regression analyses will be used to assess the associations between treatments and changes or increases in outcomes from baseline to the end of follow-up in univariate and multivariate modeling adjusted for relevant covariates.

All data will be analyzed using intention-to-treat principles. Multiple imputation by chained equations will be used to address missing data caused by loss to follow-up and non-responses. Per protocol analyses will also be performed in the participants who complete other assessments, including Hmax/Mmax, MCV, RMS, iEMG, CR, MyotonPRO, and IRT. Statistical analysis will be performed using SPSS software (version 20.0) and the significance level set at *p* < 0.05.

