### Inclusion Criteria

Participants will be qualified for inclusion when they meet the following criteria: (1) meeting the “criteria for the diagnosis of cerebrovascular diseases” adopted by the Fourth Academic Conference on Cerebrovascular Diseases in 1995 (43) and confirmed using computed tomography or magnetic resonance imaging examination of the head; (2) age between 35 and 75 years old, with a first episode > 1 month and being in a stable clinical condition; (3) the presence of hemiplegic or hemiparesis with elbow joint spasticity grade > 1, determined by MAS (31); (4) no obvious cognitive impairment; and (5) the informed consent form being completed by the patient.

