## Discussion

Stroke survivors with spasticity suffer substantial mental, physical, and financial stress. Effective spasticity treatment will likely increase their functioning and their health-related quality of life. Clinical studies (48–50) have shown that ESWT may improve the muscle spasm of stroke patients without serious adverse reactions. A meta-analysis (51) found that adding the ESWT to conventional therapy provides an additional benefit for reducing upper limb spasticity, and the results may be optimal given the ESWT at the subacute phase, but the mechanism remains unclear. Many studies conducted in recent years have been investigating the biological effects of ESWT (52–55). In the past, the mechanism by which ESWT acts on musculoskeletal diseases was assumed to be mechanical decomposition, just like extracorporeal shock wave lithotripsy. However, further clinical observations and experimental results have suggested that ESWT can promote neovascularization, the release of growth factors, the differentiation of mesenchymal stem cells, and the production of endogenous nitric oxides (15, 56, 57), which can decrease the intrinsic stiffness of connective tissue, increase muscle elongation, improve tissue microcirculation, and change the formation of neuromuscular junctions of the peripheral nervous system (55, 58, 59), to achieve encouraging clinical results.

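### The primary MAS model adjusts for baseline MAS only; adding time since stroke, which the trial must already know, could give modest extra precision and protection from chance imbalance

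*Protocol article*

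**What the plan says.** Statistical Methods names the terms of the primary comparison: a "repeated measures mixed-effect model with terms of treatment, time, and corresponding baseline values as covariates". The intervention-by-time interaction is examined first, and the analysts "then proceed to the main effects model with only group and time". Other covariates appear only in the secondary linear and logistic regressions, fitted "in univariate and multivariate modeling adjusted for relevant covariates", and these covariates are not named.

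Three other sections bear on the choice:

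- Inclusion Criteria requires patients "with a first episode > 1 month and being in a stable clinical condition". There is a lower limit on time since stroke but no upper one.
- Randomization has patients "randomly assigned to group A (active rESWT) or group B (sham-placebo rESWT), with a total of 50 patients in each". No stratification factor is described.
- The Discussion reports, from a cited meta-analysis, that "the results may be optimal given the ESWT at the subacute phase".

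**The concern.** The entry criteria allow patients a few weeks after stroke and patients years after it into the same comparison. The authors themselves cite a source that links stroke phase to the size of the ESWT benefit. Nothing in the allocation as described balances phase between arms, and the primary model does not adjust for it. The adjustment that is planned sits in secondary regressions and does not reach the primary comparison.

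If time since stroke predicts post-treatment MAS beyond what baseline MAS already carries, leaving it out enlarges the residual variance. A chance difference in phase between the arms would then also pass into the estimate uncorrected. The information is at hand: the eligibility check needs the date of the stroke, and Table 2 collects medical history at enrolment.

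**Working it through.** **Plan's own figure.** The article gives no precision or power figure for the MAS mixed model. Its only power statement, in Sample Size Calculation, concerns responder proportions: 64.5% versus 80%, two-sided alpha 0.05, power 90%, 45 per group. It cannot serve as a starting point here, because it concerns a different endpoint and does not reproduce. The pooled two-proportion formula gives n = [1.960·√(2·0.7225·0.2775) + 1.282·√(0.645·0.355 + 0.80·0.20)]² / 0.155² ≈ 174 per group, and 50 per group gives about 41% power. That is a separate matter, and no plausible covariate gain would close the gap. I therefore take an effect that the baseline-only model detects with 80% power.

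**Inputs.** From the documents: 50 per arm, N = 100. Assumed: the residual correlation r, shown over a range, and for one illustration a 50% share of subacute patients.

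**Precision.** Work in units of the residual SD given baseline MAS, treating the comparison as an ANCOVA with one post-treatment value.

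1. SE of the treatment difference = √(2/50) = 0.20.
2. Effect detectable with 80% power = (1.960 + 0.842) × 0.20 = 0.560.
3. Adding a covariate with residual correlation r multiplies the variance by v = (1 − r²) × (96/95). The second factor is the approximate price of one more covariate.
4. Power ≈ Φ(2.802/√v − 1.960). Effective sample size gain = 1/v − 1.

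| r | v | Power | Effective N gain |
|---|---|---|---|
| 0 | 1.011 | 79.6% | −1% |
| 0.1 | 1.000 | 80.0% | 0% |
| 0.2 | 0.970 | 81.2% | 3% |
| 0.3 | 0.920 | 83.2% | 9% |
| 0.4 | 0.849 | 86.0% | 18% |

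The break-even point is v = 1, that is r² = 1 − 95/96 = 0.0104, or r about 0.10. With 90 completers the powers are almost the same.

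**Chance imbalance.** With 50 per arm and unstratified allocation, the between-arm difference in a continuous covariate has a 95% range of ±1.96 × 0.20 = ±0.39 SD. The resulting shift in the unadjusted estimate is r × 0.39: about 0.04 residual SD at r = 0.1 and 0.12 at r = 0.3. The latter is about a fifth of the 0.56 above.

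If half the patients were subacute, the 95% range would be ±1.96 × √(0.25 × 2/50) = ±20 percentage points. A difference of at least 16 points would occur with probability 13% (binomial) to 16% (hypergeometric), and one of at least 20 points with probability 6% to 7%.

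**Validity check.** ANCOVA was simulated with 50 per arm, 3,000 runs per setting and an effect of 0.56.

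- Type I error of the baseline-only model was 0.050 to 0.055 across r = 0, 0.3 and 0.5.
- Adding the covariate moved power from 0.792 to 0.785 at r = 0, from 0.790 to 0.820 at r = 0.3, and from 0.776 to 0.886 at r = 0.5.

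**The case against.** The strongest answer is that nothing here is wrong. A mixed model adjusted for the baseline value of the outcome is a standard, valid primary analysis. Further covariates are often left to an analysis plan, and that plan is not shown. The validity part of this stands in full. The deferral part stands only partly, because the article does not leave the primary terms open: it lists them and places other covariates in the secondary regressions. An analysis plan that added one would depart from this text.

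A reader might infer from the Discussion that the protocol establishes time since stroke as an influential predictor. It does not. The sentence is a hedged report of a meta-analysis about how the benefit of ESWT varies with phase, which is effect modification. A main-effect covariate gains precision only if it predicts post-treatment MAS given baseline MAS. A benefit that varied by phase would produce some such association in the active arm, unless an opposite trend in controls cancelled it, but the documents do not show this.

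A reader might also infer that precision is certainly being lost, or that the comparison is biased by imbalance. Neither is supported. The value of r is unknown, and a small one is plausible: baseline MAS is already in the model, all assessments fall within a short series of three sessions, and the patients are inpatients whose actual spread of time since stroke may be narrower than the criterion allows. Chance imbalance is already covered by the error rate of the randomised comparison.

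**Conclusion.** The point holds as an efficiency improvement, not as an error or a contradiction. The primary model as written is unbiased and keeps its type I error. By omitting a variable that must already be known, it may forgo modest precision: roughly 1 to 6 percentage points of power from a base of 80% if r lies between 0.2 and 0.4, nothing at r = 0.1, and a loss of about 0.4 points at r = 0. The trade is lopsided in favour of adjusting, since the possible loss is negligible and the possible gain is modest.

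These figures rest on the assumed r, on a single-outcome approximation to the repeated-measures model, and on treating the MAS values as continuous. The imbalance probabilities also rest on the assumed 50% subacute share.

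One related wording needs care. The second-step model is described as containing only group and time. A reader might take this to mean that baseline MAS is dropped. It may equally mean only that the interaction is removed, and the text does not settle which.

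**What to change.** Before unblinding, amend Statistical Methods so that the primary MAS mixed model includes time since stroke at baseline (for example log months) as a fixed covariate. State in the same place that baseline MAS stays in every step, including the main-effects model. This applies equally to the 50 patients already recruited at manuscript submission, and it needs no new data and no change to randomisation.

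The cost is one model degree of freedom, about 0.4 points of power if the variable turns out not to be prognostic, and a minor amendment, which under Harm and Audit needs Ethics Committee approval.

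A treatment-by-time-since-stroke interaction is not needed for this change. It would have little power in 100 patients, and if it is reported at all it should be labelled exploratory.
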